# Topical sirolimus solution for lingual microcystic lymphatic malformations in children and adults (TOPGUN): study protocol for a multicenter, randomized, assessor-blinded, controlled, stepped-wedge clinical trial

**DOI:** 10.1186/s13063-022-06365-y

**Published:** 2022-07-08

**Keywords:** Lingual microcystic lymphatic malformation, Lymphangioma, Lymphatic abnormalities, Sirolimus, Mucosa, Topical treatment, Stepped-wedge design

## Abstract

**Background:**

Lingual microcystic lymphatic malformations (LMLMs) are rare congenital vascular malformations presenting as clusters of cysts filled with lymph fluid or blood. Even small well-limited lesions can be responsible for a heavy burden, inducing pain, aesthetic prejudice, or oozing, bleeding, infections. The natural history of LMLMs is progressive worsening punctuated by acute flares. Therapeutic options include surgery, laser excision, and radiofrequency ablation but all are potentially detrimental and expose to local relapse. Therefore, the management frequently relies on a “watchful waiting” approach. In complicated LMLMs, treatment with oral sirolimus, a mammalian target of rapamycin (mTOR) inhibitor, is often used. Topical applications of sirolimus on the buccal mucosae have been reported in other oral diseases with good tolerance and none to slight detectable blood sirolimus concentrations. We aim to evaluate the efficacy and safety of a 1 mg/mL sirolimus solution applied once daily on LMLM of any stage in children and adults after 4, 8, 12, 16, 20, and 24 weeks of treatment compared to usual care (no treatment).

**Methods:**

This is a randomized, multicentric study using an individually randomized stepped-wedge design over 24 weeks to evaluate topical application of a 1 mg/mL sirolimus solution once daily, on LMLM, versus usual care (no treatment), the control condition. Participants begin with an observational period and later switch to the intervention at a randomized time (week 0, 4, 8, or 12). Visits occur every 4 weeks, either in the study center or by teleconsulting. The primary outcome will be the evaluation of global severity of the LMLM on monthly standardized photographs by 3 independent blinded experts using the physical global assessment (PGA) 0 to 5 scale. Secondary outcomes will include lesion size measurement and quality of life assessment, investigator, and patient-assessed global disease and specific symptoms (oozing, bleeding, sialorrhea, eating impairment, taste modification, aesthetic impairment, pain, and global discomfort) assessment. A biological monitoring will be performed including residual blood sirolimus concentration and usual laboratory parameters.

**Discussion:**

Given the disappointing state of current treatment options in LMLMs, topical sirolimus could become firstline therapy in treating LMLMs if its efficacy and safety were to be demonstrated.

**Trial registration:**

ClinicalTrials.gov NCT04128722. Registered on 24 September 2019.

EudraCT: EUCTR2019-001530-33-FR

Sponsor (University Hospital Center of Tours – CHRU Tours): DR190041-TOPGUN

French regulatory authorities: ID RCB: 2019-001530-33

**Supplementary Information:**

The online version contains supplementary material available at 10.1186/s13063-022-06365-y.

## Background

Lymphatic malformations (LMs) are rare congenital anomalies (estimated prevalence < 0.1%) [1]. They belong to the wider group of vascular malformations, according to the International Society for the Study of Vascular Anomalies (ISSVA) 2014 classification [2, 3], as part of low-flow vascular malformations. They can be isolated or associated with other anomalies or birth defects such as Proteus syndrome or CLAPO syndrome. LMs present as clusters of cysts filled with translucid fluid or blood that can be macrocystic, microcystic, or mixed type. Any part of the skin or mucosae can be involved, with or without involvement of the underlying deep structures. At least 50% of LMs can be found in the head and neck area [4]. In this area, the buccal cavity is the most often involved, especially in medial microcystic LMs of the tongue [5, 6]. Despite their very heterogenous clinical severity and presentations, all medial microcystic LMs are classified as stage III according to de Serres et al., which implies high post-surgical relapse rate and peri-operative complications [7].

Specifically, patients with LMLMs, even those with small well-limited lesions, often experience a heavy burden because of oozing, spontaneous bleeding, infections, or even speech, chewing, or breathing impairment. An important aesthetic prejudice is also frequently reported [8, 9]. The disease’s natural history features progressive worsening, often punctuated by acute flares such as infections, bleeding, or acute swelling, sometimes secondary to lymphatic drainage-stimulating conditions such as trauma or ear-nose-throat regional infections [9].

Current therapeutic options are still limited and mostly rely on surgery or local interventional procedures. Although sclerotherapy may yield good results in macrocystic LMs, where large well-delimited cysts, this standard treatment option remains disappointing in more ill-defined infiltrative microcystic LMs, with high rates of post-surgical relapse or deep-structure iatrogenic lesions [10–12].

Complete surgical resection is rarely achievable in the oral cavity and can be tied to significant post-operative complications, such as post-operative edema, post-operative infections, delayed healing, or facial nerve palsies in deep infiltrative oral LMs [10]. Multiple partial resections may achieve functional improvement while minimizing drawbacks.

Other interventional techniques reported include CO_2_-laser excision or radiofrequency ablation, most often for superficial LMs or as combination therapy after surgery for larger LMs. However, they often lead to reduced symptoms but only very rarely achieve permanent curative results and may induce deeper tissue scarring that might hamper secondary function-preserving surgery [6].

Thus, LMLM management remains challenging, and a conservative management (“wait-and-see” approach) is frequently chosen. Iterative courses of antibiotics and steroids are started in response to acute flares or infections, with the caveat that infection-induced LMLM growth may render secondary ablation difficult.

The mammalian target of rapamycin (mTOR) is an intracellular kinase downstream from the PI3K-AKT pathway. When activated by the effect of the PI3K-AKT complex, it binds with other intracellular proteins, forming serine-threonine kinase mTOR complexes 1 and 2, which are involved in cell growth and apoptosis via protein synthesis and cell-cycle regulation [13, 14]. The PI3K-AKT-mTOR pathway is heavily involved during angiogenesis and lymphangiogenesis [15].

Known mutations in the PI3K-AKT-mTOR pathway have been discovered in both non-syndromic and syndromic lymphatic abnormalities, such as Proteus syndrome and Pi3K-related overgrowth spectrum-linked diseases (CLOVES syndrome or Klippel-Trenaunay syndrome) [16–18].

Sirolimus is a powerful inhibitor of the mTOR kinase, thereby preventing cellular growth and leading to apoptosis. It has been granted US Food and Drug Administration approval for preventing chronic allograft rejection in renal transplant recipient. In vitro, applying sirolimus to rat pancreas cancer-derived cells reduced VEGF-C expression and inhibited lymphangiogenesis; similar results were found in mice inoculated with the cells [15]. Similarly, sirolimus-treated cells from LMs showed inhibited growth [17], whether cultivated from syndromic (Proteus syndrome) or isolated LMs.

The first oral sirolimus administration as a compassionate treatment in refractory LMs was reported in 2008 in a 9-month-old boy [19] with multiorgan failure due to Proteus syndrome. Since then, sirolimus has been applied in different vascular anomalies [9, 20, 21], with 2 RCTs of LMs currently under way (NCT00975819, Adams, USA [active] and NCT02509468, [name], France [completed]) [22, 23].

However, despite an overall good safety profile (absent or mild side effects in 2 of 3 patients with vascular anomalies, including children), significant dermatologic (oral mucositis), hepatic (elevated liver enzymes, hepatitis), or hematologic side effects may occur. Grade III or IV drug-induced cytopenia is reported in up to 27% of treated patients, with some severe infectious complications also being reported [9, 20].

Hence, close clinical and biological follow-up is required, with sirolimus blood concentration monitoring. Treatment indications tend to be limited to the most severe lesions (i.e., extensive deep infiltration, aerodigestive airway involvement).

### Topical sirolimus on skin and mucosae

The first topical use of sirolimus was reported in a 2005 pilot study involving 24 patients with plaque psoriasis [24]. It has also been tried in multiple inflammatory or vascular-based skin and mucosae diseases such as oral erosive lichen planus [25], oral pemphigus vulgaris [26], port-wine stains, or tuberous sclerosis-induced facial angiofibromas [27–29].

There are few case reports describing sirolimus use in cutaneous microcystic LMs, in both children and adults, yielding promising results regarding lesion shrinking and a sharp reduction in the frequency of acute bleeding, swelling, or infectious episodes [30–32].

Mucosal topical sirolimus treatment has been reported in some inflammatory conditions. Undiluted commercial oral sirolimus solution (Rapamune®, Pfizer) had moderate effect in seven females with oral and/or genital lichen planus [25]. The tolerance was overall good, with only one treatment interruption due to local irritation. Blood sirolimus levels were monitored, with a peak sirolimus concentration of 1.5 ng/mL, well below usual therapeutic concentrations of 4 to 12 ng/mL, in only one patient with both oral and genital involvement, 2 h after treatment.

Nudelmann et al. [33] performed more extensive studies of oral sirolimus as a 0.05% mouthwash. Therapeutic sirolimus concentrations were detected in saliva up to 4 h after mouth washing, and peak blood sirolimus concentrations were from 0.2 to 1 ng/mL at 1 h after a single rinse with sirolimus mouthwash. No immediate side effects were reported, and no significant change was reported between an oral cavity examination performed by an oral medicine specialist before and 24 h after using the mouthwash.

### Objectives

Hence, we aim to perform a clinical trial (TOPical sirolimus in linGUal microcystic lymphatic malformatioN [TOPGUN]) to assess the efficacy and safety of a 1-mg/mL sirolimus solution applied once daily as a topical treatment for oral microcystic LMs with lingual involvement in children and adults compared to usual care (no treatment).

## Methods

### Trial design

TOPGUN is a randomized, open, multicenter study with an individually randomized stepped-wedge design [34] over a 24-week period to evaluate the following:Daily topical application of 1 mg/mL sirolimus solution 0.5 to 1 mL according to the size of the LMLM lesion, the experimental intervention, *versus*Usual care (no treatment), the control condition

In this design, participants are included in a cohort in which treatment is introduced at a randomized timepoint. Included participants start the intervention in a staggered fashion over time. Randomization is balanced, so each participant has the same probability of starting the intervention at a given step as any other participant over the entire study period. Four steps are planned for starting the intervention (i.e., week 0 [W0], W4, W8 and W12). Hence, 3 participants will be randomly assigned to begin the intervention on W0, 3 on W4, 3 on W8, and 3 on W12.

In order to minimize participant burden related to the follow-up visits and procedures, we tried to reduce the number of on-site visits thanks to phone calls, especially during the control period (see Tables 1, 2, 3 and 4). Similarly, blood tests may be performed in partner local laboratories, closer to patients’ homes, which will then provide results to the investigator.

**Table 1 Tab1:**
[figure not shown]
Participant timeline (group 1: treatment introduction at week 0)

^a^ For women of childbearing potential, until 3 months after study close-up

^b^ Drug dispensation: 3 bottles for 8 weeks (8w) or 2 bottles for 4 weeks (4w)

**Table 2 Tab2:**
[figure not shown]
Participant Timeline (group 2: treatment introduction at week 4)

^a^ For women of childbearing potential, until 3 months after study close-up

^b^ Drug dispensation: 3 bottles for 8 weeks (8w) or 2 bottles for 4 weeks (4w)

**Table 3 Tab3:**
[figure not shown]
Participant Timeline (group 3: treatment introduction at week 8)

^a^ For women of childbearing potential, until 3 months after study close-up

^b^ Drug dispensation: 3 bottles for 8 weeks (8w) or 2 bottles for 4 weeks (4w)

**Table 4 Tab4:**
[figure not shown]
Participant Timeline (group 4: treatment introduction at week 12)

^a^ For women of childbearing potential, until 3 months after study close-up

^b^ Drug dispensation: 3 bottles for 8 weeks (8w) or 2 bottles for 4 weeks (4w)

All patients will undergo a visit (physical, “on-the-spot” visit or via secured phoning software or phone calls, according to the step-specific participant timeline), every 4 weeks until W24, when the intervention will be stopped. Assessments before starting the intervention will be compared to those after the introduction of the intervention.

The individually randomized stepped-wedge trial design is increasingly being used in clinical practice, often in rare diseases for which patient recruitment may be difficult. Because of this very rare disease, randomizing the first topical sirolimus-treated LMLM patients seemed important to obtain high-quality evidence.

Other advantages of the stepped-wedge approach include the following [34, 35]:Each patient is his own control, hence increasing trial power with a small patient count, while taking into account a possible persisting treatment effect (contrary to cross-over designs)Being able to evaluate the effect of the time of treatment introduction and treatment duration owing to the varying treatment courses from 12 to 24 weeks.Increasing trial acceptability in this rare disease. Indeed, during the study, participants need to comply with a significantly tighter clinical follow-up than during usual care and might be reluctant to apply for trial inclusion if they believe they will not receive the experimental treatment, especially if they live far from the study center. Resorting to phone calls instead of traditional face-to-face visits also aims to address this matter.

We could not use a placebo drug because of pharmaceutical stability issues. As a result, neither the patient nor the investigator is blinded to the treatment introduction timepoint. However, the main outcome will be assessed on photographs by an independent blinded adjudication committee.

### Methods: Participants, interventions, and outcomes

#### Study setting

The study will involve 3 French hospital centers (University Hospital of Tours, Regional Hospital of Orléans and hospital Necker-Enfants maladies, Paris) that are currently involved in the treatment of vascular anomalies.

#### Eligibility criteria

##### Inclusion

Eligible patients will be at least 5 years old. They must have a diagnosis of LMLM of any stage (Wiegand 2009) [6], assessed by clinical examination, with or without an underlying syndromic malformation (e.g., Proteus or CLAPO syndrome). Deep infiltration must have been assessed by head-and-neck MRI before study enrolment.

We chose a 5-year age threshold because although LMLMs are often diagnosed before age 2 years, they might not be clinically relevant in very young children, given their natural history of progressive worsening. Also, the topical administration that requires not swallowing the oral solution might be difficult in younger children with smaller oral cavities. Finally, in this study, we can use validated quality-of-life assessment instruments (Children’s Dermatologic Life Quality Index [cDLQI]), which cannot be used for children under age 4 years [36].

##### Exclusion

Patients with any of the following conditions are not included in the study:Lymphatic malformation that requires a continued background therapy (involving deep organs)Secondary lymphatic malformations (e.g., radiotherapy-induced lymphangiectasia)Immunosuppression (immunosuppressive disease or immunosuppressive treatment)Ongoing neoplasiaActive chronic infectious disease (e.g., hepatitis B and C virus, HIV)Local necrosisLocal fungal, viral (herpes simplex virus, varicella-zoster virus, etc.) or bacterial infection on the site of the LMLM (based on clinical examination)Previous treatment with systemic or topical mTOR inhibitors within 6 months before inclusion (oral sirolimus half-life is 60 h in adults according to Summary of Product Characteristics for Rapamune®).Previous treatment with oral or topical steroids within 10 days before inclusion (half-life of corticosteroids is 12–36 h)Known allergy to one of the components of the sirolimus solutionSoybean or peanut allergyPregnant or breastfeedingFemale patients of childbearing potential not using a reliable contraceptive methodConcurrent involvement in another therapeutic trial

#### Intervention

During the observation (control) period, patients will receive usual care for their LMLM, which is no treatment at this stage of the condition.

Then, after crossing over to the experimental period, the intervention is the 1-mg/mL sirolimus oral solution (Rapamune®, Pfizer), administered once daily. If the LMLM covers below an estimated <4 cm^2^ of target area, the treatment dose is 0.5 mL, once daily. If the LMLM covers above an estimated ≥4 cm^2^ of target area, the treatment dose is 1 mL, once daily.

A total of 0.5 or 1 mL non-diluted sirolimus solution will be taken from the bottle by using the 1-use dosing syringe and applied on a standardized disposable applicator device. Then the applicator device will be gently applied, only on the LMLM, until the solution is no longer oozing from the applicator device, for at least 10 s. The patient must then not eat, drink, brush teeth, or use mouthwash for 1 h.

Applicators and syringes are to be disposed of adequately. Rapamune® bottles must be brought at every dispensation visit to assess patient observance. Syringes must not be re-used.

The treatment will be started at a randomized timepoint (W0, W4, W8, or W12) and will be taken until W24 whatever the starting time.

In case of serious adverse reactions, including local necrosis or any systemic reaction, the intervention (topical sirolimus) will be stopped. In case of local side effects, the intervention might be temporarily halted. If the patient, the sponsor, and the investigator deem it appropriate, the intervention can be resumed, at full or half-dose. In case of relapse, the lowest bearable dose will be sought; otherwise, the treatment might be stopped. If the lesion is totally removed before W24, the investigator could propose early withdrawal of the treatment. In this setting, follow-up would be according to the protocol until W24.

Participants (or together with their parents if they are < 18 years old) will be asked to keep a daily participant diary, recording information about adherence and safety data. They will be asked to bring the diary at each study visit.

At each on-site study visit, participants will be asked to provide all their used and unused study drug containers.

If a participant were to prematurely discontinue the intervention, whatever the reason, or if adherence to intervention schedule were to be imperfect, all assessments planned should be performed, including distant and on-site monthly visits and blood tests.

Regarding concomitant care, in the event of an acute flare or local or generalized infection, antibiotics may be prescribed. Systemic steroid therapy may also be prescribed along with antibiotics, for up to 3 days. However, topical immunosuppressive drugs or steroids applied on the target area, interventional procedures (sclerotherapy, laser, radiofrequency) or surgery of the target area, and systemic steroids for more than 3 days, or immunosuppressive therapy, including systemic mTOR inhibitors, are prohibited during the study. If any of the above is administered, then the investigator must be informed, and the intervention must be stopped. In any case, all assessments planned should be performed.

#### Outcomes

##### Primary outcome

The primary outcome will be the evaluation of global severity of the LMLM by 3 independent experts (i.e., adjudication committee). To this end, the experts will compare the LMLM by using a 6-point physician’s global assessment (PGA) scale. The PGA score ranges from 0 (clear) to 5 (severe).

Photographs will be taken at baseline and every 4 weeks up to W24 by using a standardized photograph protocol (3 photos: 2 front photos [distances 8–10 and 25–27 cm] and 1 side photo [distance 8–10 cm]). Patients (and their families if relevant) will be trained in the photograph protocol during the inclusion visit and will be given cardboard templates displaying distances and angles required for each photographing incidence. During on-the-spot visits in the study center, photographs will be taken by a trained research nurse or investigator. When at home, photographs will be taken by the patient themselves or their family members and sent to a secured email address. The quality of the photographs will be controlled immediately by the investigator, and the photograph protocol might be resumed until the quality is deemed satisfactory. Then, the photographs will be immediately anonymized (Fig. 1).

**Fig. 1 Fig1:**
[figure not shown]
Study diagram

The adjudication committee will be blinded to treatment allocation. They will quantify disease severity for each photograph by using the PGA scale.

There are no specific scores for LMLMs. The only existing score for head-and-neck lymphatic malformations is the Cologne Disease Score [8], but it focuses on disease-induced morbidity, with no morphology-related item, and some of its items (feeding impairment, respiration impairment) may apply to more severe lesions we do not aim to investigate. However, the PGA score is an easy-to-understand and widely used instrument in dermatology [37, 38]. We believe it relevant for this condition. The PGA score ranges from 0 (clear) to 5 (severe). A 1-point improvement versus baseline in PGA scale would already be of clinical relevance.

##### Secondary outcomes

Secondary outcomes will assess topical sirolimus efficacy and safety. They include investigator- and patient-reported outcomes, with an emphasis on quality of life and symptoms.Investigator-assessed PGA at weeks 0, 4, 8, 12, 16, 20, and 24Patient-assessed oozing, bleeding, sialorrhea, eating impairment, taste modification, aesthetic impairment, pain, and global discomfort, each on a numeric scale from 0 to 10 (0, clear; 10, very severe), at weeks 0, 4, 8, 12, 16, 20, and 24Global evolution assessed by the patient from −10 to 10 (−10, severe worsening; 0, no change; 10, complete recovery), at weeks 4, 8, 12, 16, 20, and 24Quality of life assessment (cDLQI for patients 5 to 16 years or DLQI > 16 years), at baseline, treatment introduction visit and W24Measurement of the lesion (length, width, thickness) by the investigator, at baseline, treatment introduction visit and W24Time to obtain optimal results (i.e., time from treatment introduction visit to time reaching the minimal PGA score)

Reported side effects with oral sirolimus treatment include fatigue, headache, oral mucositis, hypertension, dyslipidemia, hyperglycemia, cytopenia, and infections [nadal2016]. Topical application of sirolimus in oral diseases has also been tied to local irritation and pain [Soria2009]. Hence, to account for these reported adverse effects, safety assessments will be both clinical and biological. The clinical surveillance will include the recording of clinical local and general side effects according to the daily completion of the patient follow-up diary, questions from the investigator at each visit and physical examination and blood pressure measurement at each on-the-spot visit. Participants will also be weighed at each on-the-spot visit.

Residual blood sirolimus concentration will be monitored at week 4, week 8, and every subsequent 8th week following the beginning of the intervention (see Tables 1, 2, 3 and 4). Other routine biological safety assessments will be performed at W8, W16, and W24 of exposure, compared to baseline. Although we do not expect an important systemic diffusion, the biological surveillance measurements will mimic those used in usual systemic sirolimus treatment monitoring: complete blood count, liver (ASAT, ALAT, GGT) and renal (serum creatinine) function, lipids [triglycerides and cholesterol (i.e., total cholesterol, high-density lipoprotein cholesterol and low-density lipoprotein cholesterol estimated according to Friedewald’s formula)], and glycaemia.

Blood tests will only be used for the biological surveillance. No genetic or molecular analysis will be performed, and no specific sample conservation procedures have been designed.

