#### Statistical methods

A detailed analysis plan will be a priori defined. SAS 9.4 and R 3.3.1 (or latest versions) will be used for analysis. The level of statistical significance will be set at 5%.

The primary outcome (PGA) will be treated as a continuous variable. For analysis, we will use the model described by Hooper et al. [35] Analysis will rely on a mixed linear regression model with a random effect for participant. For each participant, we will include the 7 PGA measurements from W0 to W24 (assessed every 4 weeks).

The model will be as follows, denoting *Y*_*ijt*_ as the PGA for individual *i* = 1,.., n in sequence *j* = 1,…, T at time *t* = 0,…, *T* after randomization:$${Y}_{ij t}=\beta +{\tau}_t+{A}_{jt}+{\eta}_{ij}+{\varepsilon}_{ij t}$$

where $${\eta}_{ij}\sim N\left(0,{\sigma}_b^2\right)$$ is the participant random effect; $${\varepsilon}_{ijt}\sim N\ \left(0,{\sigma}_w^2\right)$$ is the random error; and *η*_*ij*_ and *ε*_*ijt*_ are all independent, and,$${A}_{jt}\left\{\begin{array}{c}0\ if\ sequence\ j\ is\ in\ the\ control\ condition\ at\ time\ t\\ {}{\alpha}_k if\ sequence\ j\ crosses\ to\ the\ intervention\ between\ times\ t-k\ and\ t-k+1,k\ge 1\end{array}\right.$$

The mean of PGA for an individual participant follows a trajectory with baseline *β* (mean PGA at baseline) and time effects *τ*_*t*_, *t* = 0,…,6 with *τ*_0_ = 0.

When the participant crosses over to topical sirolimus, additional effects of treatment will be estimated with *α*_1_ additional treatment effect in the first 4-week period after crossing over, changing to *α*_2_, *α*_3, …,_
*α*_6_, mean additional treatment effect at W8, W12, W16, W20, and W24 after the introduction of sirolimus respectively.

This trial has a 4-sequence design, and our primary treatment effect of interest will be α_3_, the mean difference in PGA at 12 weeks after the introduction of topical sirolimus. We will also estimate *α*_1_, *α*_2_, *α*_4_, *α*_5_, and *α*_6_, mean additional treatment effects at W4, W8, W16, W20, and W24, respectively, after the introduction of sirolimus.

Missing data will not be imputed for this analysis.

Individual trajectories of PGA will be plotted by using a spaghetti plot.

Secondary outcomes (global severity of disease and functional impairments) will be treated as continuous variables ranging from 0 to 10. We will use the same model as for the primary outcome.

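### Lesion size and DLQI/cDLQI are never measured in treated and untreated participants at the same visit, so neither can give a randomised comparison of sirolimus with usual care

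*Protocol article*

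**What the plan says.** The Secondary outcomes section presents these outcomes as measures of efficacy and safety, with particular weight on quality of life and symptoms. Lesion measurement is scheduled "of the lesion (length, width, thickness) by the investigator, at baseline, treatment introduction visit" and W24. Quality of life has the same timing: "cDLQI for patients 5 to 16 years or DLQI > 16 years), at baseline, treatment introduction visit" and W24. In the same section, the investigator PGA and the eight 0-10 patient scales are taken at all seven visits from W0 to W24.

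On allocation, Trial design states: "3 participants will be randomly assigned to begin the intervention on W0, 3 on W4, 3 on W8, and 3 on W12". Under Intervention, treatment "will be taken until W24 whatever the starting time". The Objectives set the comparison against usual care, meaning no treatment.

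Statistical methods specifies a model with a categorical effect for each visit time, a separate effect for each duration of exposure and a participant random effect. It extends that model to other outcomes as follows: "Secondary outcomes (global severity of disease and functional impairments) will be treated as continuous variables ranging from 0 to 10". Lesion dimensions and the DLQI/cDLQI are not named there.

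**The concern.** A stepped-wedge design separates treatment from time because, at some visits, some randomised groups have crossed over and others have not. An outcome that is never measured at such a visit loses that comparison, whatever analysis is chosen later.

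The two outcomes affected are the only quality-of-life instruments and the only dimensional measurement of the lesion. Time cannot be taken as neutral: the Background describes progressive worsening with acute flares. Worsening would hide a benefit in a before-after change, while a flare settling after introduction would imitate one, so even the direction of the bias is unknown. Both outcomes are also assessed unblinded, by the investigator or the participant. A reader of the results could take a before-after improvement as evidence against usual care when the data cannot supply it.

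**Working it through.** The Sample size section gives no calculation, so there is no figure to reproduce. The check is whether the schedule allows a treatment effect to be estimated.

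**Inputs.** Four groups of 3 (Trial design); starts at W0, W4, W8 and W12; treatment to W24 (Intervention); measurements at baseline, introduction and W24 (Secondary outcomes); fixed part of the model β + τ_t + α_k, where α_k is the effect 4k weeks after introduction (Statistical methods). Assumption: the introduction-visit measurement precedes the first application.

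**Step 1. Who is measured when.**

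| Group (start) | Untreated values | Value after crossover | Exposure at W24 |
|---|---|---|---|
| 1 (W0) | W0 | W24 | 24 weeks |
| 2 (W4) | W0, W4 | W24 | 20 weeks |
| 3 (W8) | W0, W8 | W24 | 16 weeks |
| 4 (W12) | W0, W12 | W24 | 12 weeks |

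Group 1 has only two values, because its baseline is its introduction visit. Observations: 3×2 + 9×3 = 33. At W0 all groups are untreated. At W4, W8 and W12 a single group is measured, untreated. At W24 all four have crossed over.

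**Step 2. Estimability as scheduled.** The parameters are β, four time effects (W4, W8, W12, W24) and α_3 to α_6, which makes 9. The distinct expected values are one each at W0, W4, W8 and W12, and four at W24, so the rank is 8. The four W24 means have to determine five unknowns. Adding any constant c to τ at W24 and subtracting c from α_3 to α_6 changes no expected value, so none of these effects is estimable. α_1 and α_2 are never observed. With one constant treatment effect there are 6 parameters and rank 5, because treatment is aliased with τ at W24.

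The constant c cancels in differences such as α_6 − α_3, so comparisons of duration at W24 are estimable and randomised.

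**Step 3. Contrast with the PGA schedule.** 12×7 = 84 observations, 1 + 6 + 6 = 13 parameters, rank 13: every α_k is estimable.

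**Step 4. Add W12 in all groups.** At W12 the groups have 12, 8, 4 and 0 weeks of exposure. Observations: 42. Parameters: 1 + 4 + 6 = 11. Distinct expected values: 1 + 1 + 1 + 4 + 4 = 11, so full rank. α_3 is group 1 minus group 4 at W12. That fixes τ at W24, and the other effects follow.

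**Step 5. Precision of α_3 with W12 added.** In total-SD units this is a baseline-adjusted difference between two groups of 3: SE = √[2(1 − ρ²)/3]. The document gives no within-participant correlation ρ, so a range is assumed.

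| ρ | SE | 1.96 × SE |
|---|---|---|
| 0.3 | √(2×0.91/3) = 0.78 | 1.53 |
| 0.5 | √(2×0.75/3) = 0.71 | 1.39 |
| 0.7 | √(2×0.51/3) = 0.58 | 1.14 |
| 0.9 | √(2×0.19/3) = 0.36 | 0.70 |

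Measuring at all seven visits gives an SE of 0.58, 0.54, 0.45 and 0.27 at the same correlations. These figures assume 12 complete participants on one scale.

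**The case against.** A reader might infer that the randomisation does nothing for these outcomes and that only an uncontrolled before-after change can be reported. The documents do not support that. At W24 the four randomised groups differ in exposure, and Trial design names timing of introduction and treatment duration as things the design should evaluate. Groups 2 to 4 also have two untreated values each, which carry some information on drift. This limits the claim but does not remove it: comparing durations is not comparing sirolimus with no treatment. The untreated values reach only to W12, so carrying them to W24 needs an assumed time trend that these outcomes cannot test.

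A reader might also infer that the planned analysis is faulty. It is not, as far as stated: Statistical methods does not assign these outcomes to the stepped-wedge model, and Trial design speaks of comparing assessments before and after introduction. The weakness lies in the measurement schedule.

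The sparse schedule is partly deliberate. Trial design and the Discussion limit on-site visits because patients may live far away. That is a fair reason for lesion measurement, but a weak one for a questionnaire. Related constructs keep a concurrent comparison through the blinded photographic PGA, the investigator PGA and the patient scales. The gain in precision from extra visits is modest. Finally, Tables 1-4 hold the detailed schedules and are not shown, so an extra measurement there cannot be excluded, although the text lists only three times.

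**Conclusion.** The point holds for the comparison with usual care. On the stated times, lesion size and DLQI/cDLQI have no visit with both treated and untreated participants, and no effect against no treatment is estimable (rank 8 of 9; 5 of 6 with a constant effect). This is algebraic and needs no assumed SD or correlation. It rests on three conditions: time is left free, as in the protocol's model; the introduction measurement is taken before treatment; and Tables 1-4 add no further measurement.

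An unblinded before-after change confounded with time since randomisation remains, with a randomised comparison of 12 to 24 weeks of exposure at W24. The primary outcome is unaffected. The schedule should be changed because these are listed as efficacy outcomes in a trial set up against usual care, and the quality-of-life part is inexpensive to correct.

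**What to change.** **Quality of life.** For participants still to be followed, collect the DLQI/cDLQI at the existing 4-weekly contacts alongside the 0-10 scales, remotely where the contact is remote, or at least at W12 in all four groups. Analyse it with the stepped-wedge model, and state in advance how the two age-specific instruments are handled.

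**Lesion size.** Measure at W12 in every group where that contact is already on site or an extra visit is acceptable. Otherwise label lesion size a descriptive before-after outcome that supports no claim against usual care.

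**Participants already past W12.** Report their values on both outcomes as descriptive.

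**Cost.** A protocol amendment, a short questionnaire per contact and possibly one on-site visit. The return is limited. Trial status reports five participants included, two of whom had completed, so of the 12 planned, 7 were still to be included and up to 3 more were in follow-up. Fewer than 12 will contribute, and the SEs above are therefore best cases.
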